## 4 STUDY DESIGN

### 4.1 OVERALL DESIGN. LOW-INTERVENTION CLINICAL TRIAL.

NeoCirc-002 is a single center, dose finding trial to define the minimum effective dose of dobutamine to treat early hemodynamic insufficiency in the preterm infant (less than 33 completed weeks' gestation), defined as presence of low SVC flow (<51 ml/k/min) within the first 72 hours from birth.

The trial is a low-intervention clinical trial since dobutamine is the standard treatment for circulatory failure in preterm infants during transitional circulation, the dosages studied are within the standard therapeutic range, and the diagnostic supplementary procedures are in routine clinical practice.

### 4.2 SCIENTIFIC RATIONALE FOR STUDY DESIGN AND DOSE

As other catecholamines, dobutamine is always administered in continuous i.v. infusion, preferably through a central line.

Recent data from clinical and pre-clinical investigations, and clinical experience, indicate that dobutamine can be safely up titrated from a starting dose of 5 µg/kg/min in steps of 5 µg/kg/min in rather flexible timing within limits of up to 20 µg/kg/min; and that there is until now no evidence that dobutamine could introduce harm in newborn babies using this treatment scheme (11, 28, 41).

Although the information is scarce, there is a wide range in threshold doses of dobutamine needed to increase heart rate, blood pressure or cardiac output in children and adolescents (31-33), so that individual titration is extremely important. The minimum dobutamine dose at which a pharmacodynamic effect has been shown in neonates is 10 µg/kg/min (15-17, 19, 23, 25, 26,

28). In two RCT conducted in preterm infants on the effect of dobutamine on SVC flow (11, 28), the lowest dobutamine dose that was evaluated was 10 µg /kg/min.

Results from PK sub-study NeoCirc-001A revealed high inter-individual PK variability regarding dobutamine elimination half-life and consequently, time to reach steady-state that ranged from 15 min to 180 min (35). Due to this important inter-individual variability, there is still a need to confirm the lower effective dose in very preterm neonates; therefore, the proposed study will cover dobutamine dose-range from 5 to 20 µg /kg/min.

#### 4.4 END OF STUDY DEFINITION

An infant is considered to have completed the study if he or she has completed all phases of the study including the last visit or the last scheduled procedure shown in the Schedule of Activities (SoA), Section 1.3.

The end of the study is defined as completion of the last visit or procedure shown in the SoA in the trial.

## 5 STUDY POPULATION

### 5.1 INCLUSION CRITERIA

Infants are eligible to be included in the study only if they meet **all** the following criteria:

- Born up to 32(+6) weeks gestation
- Presence of haemodynamic insufficiency, defined as SVC flow <51 ml/kg/min.
- Provision of signed and dated informed consent form by father/mother or legally designated representative, which can be given antenatally as described in section 5.4.

Three notes of caution are necessary with respect to inclusion of infants into this trial:

- The treating physician needs to be at “clinical” equipoise on providing the proposed trial of dobutamine-treatment to the infant, which can be justified as explained in section 2.1 above.
- To avoid over treatment, the treating physician needs to fully understand the determinant of the pathophysiology of circulatory impairment and use clinical judgment to decide treatment. For example, during severe congenital anaemia a baby meeting the inclusion criteria will not be included and will instead get the required blood volume replacement first; and only afterwards could be considered for inclusion if still eligible.
- Deferred informed consent and prior informed assent (opt-out with enrollment as default) are plausible in this condition because it is in accord with Article 35 of the Regulation of the European Union on Clinical Trials (Regulations (EU) no536/2014), that states: Informed consent to participate in a clinical trial may be obtained, and information on the clinical trial may be given, after the decision to include the subject in the trial, provided that this decision is taken at the time of the first intervention on the subject, in accordance with the protocol for that clinical trial and that all the following conditions are fulfilled:
  - Urgency of the situation, caused by a sudden life-threatening or other serious medical condition
  - Scientific grounds to expect that participation of the subject in the trial will have the potential to produce a direct clinically relevant benefit for the subject resulting in a measurable health-related improvement or in the diagnosis of its condition

- It is not possible within the therapeutic window to supply all prior information to and obtain prior informed consent from his/her legally designated representative
- The investigator certifies that he or she is not aware of any objections to participate in the clinical trial previously expressed by the legally designated representative
- The clinical trial relates directly to the subject's medical condition because of which it is not possible within the therapeutic window to obtain prior informed consent from the legally designated representative and to supply prior information, and the clinical trial is such a nature that it may be conducted exclusively in emergency situations
- The clinical trial poses a minimal risk to, and imposes a minimal burden on, the subject in comparison with the standard treatment of the condition.

Informed consent shall be sought to continue the participation of the subject in the clinical trial, and information on the clinical trial shall be given to the parent or the legally designated representative.

## 5.2 EXCLUSION CRITERIA

Patients will be excluded from the study if they meet any of the following criteria:

- Neonates considered non-viable, with a clinical decision not to provide life support
- Infants with severe congenital hydrops fetalis needing chest or peritoneal drainage before recruitment
- Infants already on dobutamine treatment
- Infants with congenital malformations likely to affect cardiovascular adaptation (including: congenital diaphragmatic hernia, gastroschisis or congenital heart defects).
- Infants carrying chromosomal anomalies
- Lack of parental signed informed consent

## 5.3 SCREEN FAILURES

Screen failures are defined as participants whose father/mother or legally designated representative consent to participate in the clinical trial AND undergo screening assessments to see if they can enter the study, BUT are not subsequently randomly assigned to the study intervention or entered in the study. The data from the Screening Visit should be recorded into the eCRF for the screen failures.

## 5.4 STRATEGIES FOR RECRUITMENT AND RETENTION

By definition, this is a trial conducted on a vulnerable population, both from the perspective of the subject but also from the point of view of the parents. In many instances, preterm birth is produced suddenly, without an anticipated cause. Even in the case of antecedents supporting the risk, parents are never prepared for a preterm delivery. In particular, the most immature preterm infants will need intensive care treatments to help their breathing, and many of them will need interventions to improve their circulation soon after birth.

This is a stressful time for parents and families. Coping with all the information provided at this early stage is difficult for parents. For this reason, a strategy for recruitment is in place to avoid

overloading parents with information during the critical period after birth when they are most vulnerable:

- Whenever possible parents will give written informed consent antenatally after explanation of the aims, methods, benefits and potential hazards of the trial. The implications of the trial to the neonates enrolled should be clearly explained by the local research team as part of the informed consent process.
- Parents that have not yet given written informed consent for the trial will be approached as soon as possible after the birth of a baby between a gestational age of 24 weeks (+0 days) and 32 weeks (+6 days) and postnatal age <72 hours in risk of haemodynamic insufficiency; and provided with the relevant parental information.

With this strategy many parents would have already given signed informed consent antenatally.

Only those babies with existing signed informed consent can be enrolled into the trial (randomized and receive the trial intervention).

Given that the condition can be considered as an emergency in some situations, and treatment should be indicated if circulatory failure is present regardless of the clinical trial, deferred informed consent and prior informed assent (opt-out with enrollment as default) would be applicable, in accord with Article 35 of the Regulation of the European Union on Clinical Trials (Regulations (EU) no536/2014) (see section 5.1). However, it is worth noting that deferred consent and opt-out are only allowed in a handful of very specific situations that will need to be fully described at a site level in agreement with the PI and local hospital policies.

## 6 STUDY INTERVENTION

### 6.1 STUDY INTERVENTION ADMINISTRATION

#### 6.1.1 Study Intervention Description

Once the patient has fulfilled the inclusion criteria, he or she will be allocated to a dosage regimen according by the study statistician. The statistician will be informed about the therapeutic response observed for re-estimation of the posterior probability of success after each cohort of 3 patients. The choice of allocation will be decided according to dose with the posterior probability closer to the target probability (80%).

The dobutamine solution is commercially available dobutamine (Dobutamine Generis, concentration 12.5 mg/mL). It will be impossible to blind carers or assessors to the dose used.

#### 6.1.2 Dosing and Administration

The study medication for infusion will be prepared and administered with strict standardisation of the administration system to minimise systematic errors due to differences in infusion set-ups. This will ensure the precise time at which dobutamine enters the body can be recorded (t0).

The infant's treatment will be guided by the responsible physician who will use the study medication under the premise of keeping a minimum time of 60 minutes from the effective infusion of dobutamine (t0) for PD assessment.

Once the primary PD variable has been assessed further management will be at the discretion of the attending physician. Therefore, if there is no PD response according to protocol with the allocated starting dose, or even if there were, the clinical situation of the patient so recommends it, the responsible physician decide on further treatment (Rescue treatment in section 6.2.1). However, clinicians are encouraged to consider the up-titration to maximum dobutamine dose first, to try to maintain the infant in the study drug as long as possible, if it is the best option for the infant.

Any changes to the treatment strategy will be documented by the responsible physician.

### 6.1.3 Individual and Global Safety Parameters

In addition to rescue treatment in the absence of a clinical response to the study intervention, as described in section 6.4.1, the following safety parameters have been established to safeguard infants participating in the clinical trial.

A change of dose is allowed during the waiting time for clinical response, if any of the following **Individual Safety Parameters** are exceeded:

- Heart rate rises above 200 bpm.
- Mean blood pressure rises above pre-established values (Table 4)

**Table 4.** *Accepted upper limits of blood pressure according to GA and day of life*

|       | Day of life 1 |           |      | Day of life 2 |           |      | Day of life 3 |           |      |
|-------|---------------|-----------|------|---------------|-----------|------|---------------|-----------|------|
| GA    | Systolic      | Diastolic | Mean | Systolic      | Diastolic | mean | Systolic      | Diastolic | Mean |
| 24    | 46            | 33        | 37   |               |           |      |               |           |      |
| 26    | 50            | 35        | 40   |               |           |      |               |           |      |
| 28    | 55            | 37        | 43   |               |           |      |               |           |      |
| <28   |               |           |      | 50            | 36        | 41   | 52            | 37        | 42   |
| 30    | 58            | 39        | 45   |               |           |      |               |           |      |
| 32    | 60            | 41        | 47   |               |           |      |               |           |      |
| 33    | 63            | 43        | 49   |               |           |      |               |           |      |
| 28-32 |               |           |      | 61            | 44        | 50   | 65            | 45        | 52   |

In case of having a dose evaluation out of schedule (outside the 60 minutes intervals) due to a safety alert that triggers a dose modification, the infusion start time of the newly modified dose will be considered the 0 min time for a new 60 minutes dose evaluation.

The following **Global Safety Parameters** will also permit a change of dose during the waiting time for clinical response and may trigger a toxicity alert and halt of the trial in one or more clinical sites:

- Expected percentage of patient presenting safety issues:
  - Blood pressure above individual safety thresholds: < 20%
  - Heart rate above safety threshold: <15%

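### Section 6.1.3 lets trial-level safety percentages permit a dose change during the 60-minute evaluation of an infant who is within its own safety limits

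*Protocol*

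**What the plan says.** Section 6.1.3 of the protocol has two layers of safety rule.

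- **Individual.** "A change of dose is allowed during the waiting time for clinical response, if any of the following" Individual Safety Parameters are exceeded: a heart rate above 200 bpm, or a mean blood pressure above the value in Table 4. After an unscheduled dose change prompted by a safety alert, "the infusion start time of the newly modified dose will be considered the 0 min time for a new 60 minutes dose evaluation".
- **Global.** The Global Safety Parameters "will also permit a change of dose during the waiting time for clinical response and may trigger a toxicity alert" and a halt. Only two are listed, both as expected percentages of patients: "Blood pressure above individual safety thresholds: < 20" per cent and "Heart rate above safety threshold: <15" per cent. Neither has a denominator, a minimum number of infants or a review time.

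Section 6.1.2 has the physician use the study drug "under the premise of keeping a minimum time of 60 minutes from the effective infusion of dobutamine (t0) for PD assessment". Section 3 ties the primary endpoint to the echocardiograms at 1 and 3 hours on the dose the infant was allocated. Section 6.1.1 has the statistician informed of responses for "re-estimation of the posterior probability of success after each cohort of 3 patients", with a maximum of 30 infants (section 9.1.1).

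**The concern.** A percentage across infants is not a finding in the infant being treated. An infant above its own heart-rate or blood-pressure limit already qualifies for a dose change, so the global sentence gives that infant nothing. What it adds, on its wording, is permission to change the dose in an infant with no exceedance because other infants had one.

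If that permission is used, the 60-minute clock restarts on the new dose and the infant yields no evaluation of the allocated dose. In a trial of at most 30 infants whose aim is the minimum effective dose, each lost or misattributed response matters. With no minimum number of infants, the permission could also open on a single early event.

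**Working it through.** **Inputs from the protocol:** limits of 20% and 15%; cohorts of 3; maximum 30; target success probability 80%; efficacy row 45/70/80/90/95% for 5/7.5/10/12.5/15 micrograms/kg/min. The protocol gives no derivation of the two limits, so there is no stated figure to reproduce.

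**Assumptions:** the percentages are running shares reviewed after each cohort of 3. A limit is reached when the observed share is no longer below it. True exceedance rates are 5% or 10%, all inside the limits. The protocol gives no exceedance rates.

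**Step 1: smallest counts.** 1/3 = 33.3%, above both 15% and 20%. One heart-rate event in the first 3 infants therefore passes the heart-rate limit, and one blood-pressure event passes the blood-pressure limit. 1/6 = 16.7% is still above 15% but below 20%. At n = 3, 6, ..., 30 the smallest counts reaching a limit are:

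- heart rate: 1, 1, 2, 2, 3, 3, 4, 4, 5, 5
- blood pressure: 1, 2, 2, 3, 3, 4, 5, 5, 6, 6

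**Step 2: first cohort.** P(at least 1 of 3) = 1 - (1 - p)^3. At p = 0.05 this is 1 - 0.95^3 = 14.3%; at p = 0.10 it is 1 - 0.90^3 = 27.1%.

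**Step 3: any of the ten reviews.** Carrying the binomial distribution of the running count through the ten reviews, and removing paths that reach the limit, gives the chance of ever reaching it:

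| True rate | Heart rate (15%) | Blood pressure (20%) |
|---|---|---|
| 5% | 30% | 18% |
| 10% | 58% | 41% |

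With both rates equal and independent, the mean number of the 30 infants treated while either limit stands breached is 3.1 at 5% and 9.4 at 10%.

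**Step 4: effect on the selected dose.** This uses a simulated continual reassessment design: power model, skeleton and truth equal to the efficacy row, normal prior variance 1.34 (assumed), cohorts of 3, n = 30, start at 5, no skipping, 4,000 runs. A used permission means one step down. The Monte Carlo standard error near 59% is sqrt(0.59 x 0.41 / 4000), about 0.8 points.

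| Scenario | Choose 7.5 | Choose 10 | Choose 12.5 |
|---|---|---|---|
| Permission never used | 21% | 59% | 20% |
| Always used, 5% rates, credited to allocated dose | 16% | 58% | 25-27% |
| Half use, 10% rates, credited to allocated dose | 13% | 59% | 27-28% |
| Always used, 10% rates, credited to allocated dose | not listed | 50-52% | 35% |
| Always used, responses dropped (5%; 10% rates) | not listed | 57%; 53% | not listed |
| Always used, credited to dose given (5%; 10% rates) | not listed | 61%; 64% | not listed |

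Ranges reflect separate runs of the simulation. The drift is upward because a response at the lower dose, which succeeds less often, is counted against the higher one.

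**The case against.** The protocol nowhere states outright that an infant within its limits may have its dose changed. That follows from reading *also* literally, and the drafters may have meant no more than a trial-level alert. Section 6.1.3 can also be read as a specific safety exception to the general 60-minute premise of section 6.1.2. The synopsis entry on PK assessments already foresees the target effect being reached on a different dose. Review after each cohort of 3 is an assumption: section 6.1.1 applies those cohorts to the efficacy response only. How a response on a changed dose enters the model may be set out in an analysis plan that is not shown.

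These points limit the size of the problem; they do not remove it. The sentence grants the permission on its face, and the individual rule leaves it no other work to do. A safety exception is reasonable for an infant with a safety signal, but this one applies without any signal in that infant.

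A reader might infer that one affected infant in the first cohort breaches both limits. It does so only if it has both a heart-rate and a blood-pressure event. A reader might also infer that the dose recommendation is compromised. The text only permits a dose change and says an alert *may* follow. If the permission is never used, the primary result is untouched, and crediting responses to the dose given costs nothing in the simulation.

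**Conclusion.** The wording should be corrected. Read literally, section 6.1.3 conflicts with the 60-minute minimum in section 6.1.2 and with the allocated-dose endpoint in section 3, and it adds no protection for an infant over its own limits. On the assumed running review, the permission would open in a sizeable share of trials even when true exceedance is well inside the limits: about 30% (heart rate) and 18% (blood pressure) at a true 5%.

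The effect on dose selection is conditional and mostly small. At 5% rates, with the permission always used and responses credited to the allocated dose, correct choice of 10 moves only from 59% to 58%, and the shift to 12.5 comes mainly from 7.5. A material loss, to about 50-52%, needs 10% rates for both parameters, use in every eligible infant and crediting to the wrong dose together. Actual use is unknown.

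The point does not extend to replacing the percentages with stricter event counts. Counts requiring an 80% posterior probability that the limit is exceeded (priors Beta(0.3, 1.7) for heart rate and Beta(0.4, 1.6) for blood pressure) would cut the chance of an alert from 91% to 62% at a true heart-rate rate of 20%, and from 92% to 57% at a true blood-pressure rate of 25%. An early, discretionary alert is a defensible cautious choice in these infants.

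**What to change.** Replace the sentence that introduces the Global Safety Parameters in section 6.1.3 with:

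*The following Global Safety Parameters may trigger a toxicity alert and halt of the trial. They do not by themselves permit a change of dose during the waiting time in an infant whose Individual Safety Parameters are not exceeded; during an alert the dose for the next infants is reviewed before allocation.*

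Add that any response observed after a safety-driven dose change is credited in the dose-finding model to the dose actually given, not to the allocated dose. Section 6.1.2 already provides that "Any changes to the treatment strategy will be documented by the responsible physician", so the dose changes are on record.

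The cost is two sentences. The downside is that a physician can no longer cite the trial-level percentage alone to change the dose within the 60 minutes. Individual limits, rescue treatment and withdrawal by the investigator stay as they are, and so do the 15% and 20% alert limits.

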| Allocation to dose regimens:       | Participants will be allocated to a dosage regimen by the study statistician.

The statistician will be informed about the therapeutic response observed for re-estimation of the posterior probability of success after each cohort of 3 patients. The choice of allocation will be decided according to dose with the posterior probability closer to the target probability (80 %).                                                                                                                                                                     |
| Stopping rules                     | 
 
1. the planned number of 30 subjects is reached;
 
2. estimated efficacy is too low for all dose levels;
 
3. suitable estimation of the first dose is obtained, based on the predictive gains (mean and maximum) of further patients' inclusions on the response probability and on the width of its credibility interval lower than 5%.
 
                                                                                                                                                        |

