## 2.4 RISK/BENEFIT ASSESSMENT

### 2.4.1 Known Potential Risks

Safety data on dobutamine use in neonates have not been systematically evaluated in RCTs, either in preterm or term newborns. Reported side effects of dobutamine in small RCTs conducted in preterm infants support the notion that it is well tolerated (11, 22-28).

RCTs comparing dopamine and dobutamine to treat systemic hypotension or low SVC flow found no differences on percentage change in heart rate (8, 36); however, cardiac arrhythmia was not systematically evaluated (36). Dobutamine-induced increase in heart rate may limit the use of high doses in some neonates. In addition, drug-induced decrease in the compliance of the myocardium as a result of significant increase in the myocardial tone may result from dobutamine use. Dopamine, but not dobutamine, has been shown to cause transient (reversible) reduction in serum levels of thyroid stimulating hormone, thyroxine and prolactin (27). No differences on short-term neonatal outcomes (mortality, structural brain damage, necrotizing enterocolitis, retinopathy of prematurity or chronic lung disease) were found, although follow-up of these variables is not complete in all trials. However, in a therapeutic exploratory trial conducted in preterm infants below 30 weeks' gestation who had low SVC flow in the first 12 h, the mortality rate in the dobutamine group was higher than the dopamine group but the difference was not statistically significant (28, 30).

Very recently an apoptotic effect of dopamine and dobutamine on neutrophils of 15 preterm infants has been shown, with the apoptotic effect of dopamine being higher than that of dobutamine (37). The implication of this finding for the benefit-risk analysis can only be assessed in the light of long-term follow-up.

The safety of dobutamine in the term infant, either with hypotension or low SVC flow, has not been tested in RCTs.

The Summary of Product Characteristics of commercially available dobutamine includes a listing of adverse events reported during exposure to dobutamine in adults. The following data relates to adults and may be relevant to neonates.

Evaluation of undesirable effects is based on the following frequency scale:

- Very common:  $\geq 1/10$
- Common:  $\geq 1/100$  to  $1/10$
- Uncommon:  $\geq 1/1,000$  to  $1/100$
- Rare:  $\geq 1/10,000$  to  $1/1,000$
- Very rare:  $< 1/10,000$

- Not known: cannot be estimated from the data available

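### The trial-level heart-rate and blood-pressure limits are raw percentages not tied to dose and do not enter allocation, so no stated safety result keeps the next cohort off a dose

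*Protocol*

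**What the plan says.** Section 6.1.3 lists two global safety parameters, each a share of patients: "Blood pressure above individual safety thresholds: < 20" per cent and "Heart rate above safety threshold: <15" per cent. They are introduced as expected percentages. They carry no dose level, minimum number of infants, review schedule or measure of uncertainty. Two consequences follow from exceeding them. A dose change is permitted in infants still waiting for a response, and the excess "may trigger a toxicity alert and halt of the trial in one or more clinical sites". The individual limits in the same section (heart rate above 200 bpm, or mean blood pressure above a tabulated value) allow a dose change for that infant.

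Allocation is described in 6.1.1 and the synopsis. After each cohort of 3, "The statistician will be informed about the therapeutic response observed", and the next dose is the one whose posterior probability of success lies nearest 80%. The three stopping rules in the synopsis are reaching 30 infants, "estimated efficacy is too low for all dose levels", and a sufficiently precise estimate.

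Section 2.4.1 states that "Dobutamine-induced increase in heart rate may limit the use of high doses in some neonates". Section 10.1.2 lets the sponsor stop the trial for unacceptable risk, without a number.

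**The concern.** The protocol expects heart-rate toxicity to depend on dose, yet its numeric limits ignore dose and its dose-choosing rule ignores safety. Followed as written, the rule can send the next cohort back to a dose with excess heart-rate or blood-pressure events, because nothing stated enters that decision except response.

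The limits cannot fill this gap as they stand. A crossing does not say which dose produced it. If the percentage is read early, one event is enough to cross. Acting on every crossing would interrupt many trials whose true rate lies inside the sponsor's own limits. Not acting leaves the allocation rule unchanged. At stake is which starting dose the next three very preterm infants receive.

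**Working it through.** **The plan's own figure.** The one design output stated (9.1.1) is the expected number of infants per dose, 5/9/12/4/0, total 30. A one-parameter power-model continual reassessment simulation used efficacies 45/70/80/90/95%, target 80%, cohorts of 3 and N = 30. The protocol does not give the prior variance (1.34 assumed), the start dose (5 microg/kg/min) or a skipping rule (no skipping upwards). The result was 3.8/10.1/12.3/3.7/0.0, within 2 infants at every dose. The protocol states no operating characteristic for the safety limits.

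**What crosses a limit.** A limit is met only while the observed share is below it, so crossing means k/n ≥ 0.15 (heart rate) or ≥ 0.20 (blood pressure).
- n = 3: one event is 1/3 = 33.3%, above either limit.
- n = 6: one event is 1/6 = 16.7%, above 15% but below 20%.
- n = 30: crossing needs 5 heart-rate events (16.7%) or 6 blood-pressure events (20%).

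**Chance prompts.** Assumption: pooled reading at n = 3, 6, ..., 30. For heart rate, P(crossed by infant 6) = 1 − (1 − p)^6, which is 1 − 0.95^6 = 0.265 at p = 5% and 1 − 0.90^6 = 0.469 at p = 10%. An exact recursion on the cumulative count gives the chance of ever crossing:

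| True rate | Heart-rate limit | Blood-pressure limit |
|---|---|---|
| 5% | 0.299 | 0.180 |
| 10% | 0.578 | 0.407 |

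Most heart-rate crossings occur in the first 6 infants (0.265 of 0.299, and 0.469 of 0.578).

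**A by-dose check, as illustration.** Take a prior worth one infant, centred on the limit L. With x events in n infants at a dose, the posterior is Beta(L + x, 1 − L + n − x). Flag the dose if P(rate > L) exceeds 0.95.
- Heart rate: 1/3 gives 0.69 and 1/6 gives 0.45 (no flag); 2/3 gives 0.958, 3/6 gives 0.964 and 4/9 gives 0.973 (flag).
- Blood pressure: 2/3 gives 0.932 (no flag); 3/3 gives 0.996 and 4/6 gives 0.989 (flag).

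**Effect on allocation.** The same model was run with a start at 5 or at 10 microg/kg/min, true efficacies as planned and nobody acting on alerts. Doses of 12.5 or above are used in 36% (start 5) or 63% (start 10) of trials.
- *Extreme case: heart-rate exceedance 80% at 12.5 and above, none below.* In the trials that use those doses, mean infants started there fall from 12.9 or 12.2 to 3.3 with the by-dose check. Over all trials that is 0.36 × 12.9 = 4.6 to 0.36 × 3.3 = 1.2, or 0.63 × 12.2 = 7.7 to 0.63 × 3.3 = 2.1. The pooled limit fires in 88% or 96% of the trials that use those doses.
- *Moderate case: 40% at 12.5 and above, 5% below.* In the trials that use those doses, infants started there fall from 12.7 or 12.2 to 7.3 or 6.8. The by-dose check fires in 64% to 68% of them and the raw percentage in 78% to 87%. Where the raw limit fires, the first alert comes before any infant has had 12.5 in 35% or 20%.
- *No excess: true rate 10% at every dose.* The check flags some dose by chance in 9% to 11% of trials for heart rate and 0.7% for blood pressure. For heart rate it blocks every dose in 0.3% to 3.0%.

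The share of trials reaching 12.5 depends on model details that the protocol does not fix. The reproduction of the plan's figure, which plugs in the posterior mean of the model parameter, puts 3.7 (start 5) or 4.6 + 0.2 = 4.8 (start 10) infants at 12.5 or above, averaged over all trials.

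**The case against.** The strongest case against is that the limits are an expected percentage with discretionary consequences, in a trial of standard treatment within the usual dose range (4.1). Individual limits protect each infant, a global crossing permits dose changes in infants on treatment, and the sponsor can stop the trial. Review timing and minimum numbers may sit in an analysis or monitoring plan that is not shown. All of this stands, and it keeps the point minor. It does not meet the narrower point: the protocol itself fixes an allocation rule without a safety term, and none of these safeguards governs the next cohort's dose.

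Several stronger readings are tempting, and the documents do not support them:
- *One event halts the trial.* The wording is permissive, and no schedule of safety reviews is stated.
- *One event crosses both limits.* A heart-rate event counts only against the heart-rate limit and a blood-pressure event only against its own, unless one infant has both.
- *Pooling usually hides an excess confined to high doses.* In the extreme case the pooled limit still fires in 88% to 96% of trials using those doses. What it lacks is identification of the dose.
- *The dose at the event is lost.* Up-titration is encouraged ("clinicians are encouraged to consider the up-titration to maximum dobutamine dose first") only after the primary assessment, and treatment changes are documented (6.1.2). During the waiting time the running dose is therefore the allocated one or a recorded modification. The adverse-event fields in 8.3.5 do not list the dose, and 8.1.2.2 records only the 72-hour maximum, so a small gap remains for later events.

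The objection that the by-dose check is weaker than the raw percentage for a moderate excess is also correct. It is a reason to keep both.

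**Conclusion.** The point holds as a minor design weakness. The numeric limits are not tied to dose, allocation depends on response alone, and no stated safety result bars a dose from the next cohort.

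The limits' poor behaviour as a rule (30% to 58% chance crossings for heart rate and 18% to 41% for blood pressure, at true rates of 5% to 10%) rests on the assumed pooled reading after every cohort of 3. It shows that the raw percentage can serve only as a prompt.

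A reader might take the fall from 12 or 13 infants to about 3 as the expected benefit of a by-dose check. It is an upper bound. It applies only to trials that use 12.5 or above, and over all trials it is roughly 5 to 8 infants falling to 1 or 2. It also assumes an extreme excess confined to those doses, for which the protocol gives no evidence, and that nobody acts on the pooled alert. It counts starting doses only, so infants titrated up from lower doses are left out.

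**What to change.** Keep the sponsor's percentages and change four things.

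1. At each existing cohort-of-3 review, before the next allocation, tabulate heart-rate and blood-pressure exceedances by the dose running at the event as well as pooled, and give the table to the allocating statistician.
2. Do not allocate the next cohort to a dose, or a higher one, whose probability of exceeding the limit passes a cut-off set by the sponsor. The Beta rule with 0.95 shown above is one example. State who decides if every dose is barred.
3. State that the raw pooled percentage is a prompt for review, and keep it, because it picks up a moderate excess more often than the by-dose check.
4. Add one eCRF entry for each exceedance: time, value and dose running.

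The reference to one or more sites in 6.1.3 can be deleted, since the trial has a single centre.

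The cost is protocol wording, one eCRF entry and a short table at reviews that already take place. The downsides are slightly more work per review and a chance heart-rate flag in about 9% to 11% of trials at a true 10% rate.
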